### Trial governance

1.5

The EMBOLDEN research team and a Strategic Guiding Council (SGC) will oversee the trial. It is anticipated that the SGC will include 26 members (18 service providers, 8 older adults). The SGC will engage older adult citizen partners and health and social service providers to co-design the intervention, guide implementation and refinements, and inform the evaluation and scalability assessment plan. The SGC will also be engaged in knowledge mobilization (e.g., developing key messages, presentations, peer-reviewed publications, lay-language summaries).

During the trial, the EMBOLDEN team will establish neighborhood-specific Community Advisory Boards (CAB), which will inform local adaptations and help address implementation challenges as they arise (e.g., recruitment, retention, interventionist-identified needs). The SGC will help to identify and recruit CAB members. CABs will comprise 6–8 older adult citizens and community providers (3–4 of each) within each identified neighborhood cluster (i.e., 2–3 neighborhoods geographically co-located). CAB members will provide input on necessary adaptations required to tailor to their local neighborhoods, be informed of trial outcomes as they are available, help interpret findings, and develop local knowledge translation strategies.

## Methods and analysis

2

### Participants, interventions, and outcomes

2.1

#### Study setting

2.1.1

Participants will be recruited from 10 community settings in urban neighborhoods identified as areas of health inequity in the cities of Hamilton and Toronto in Ontario, Canada. The neighborhoods will be selected through a consultative process with SGC and CABs and informed by our completed environmental scan (26). Potential neighborhoods were identified in the scan using 2016 Census Tract (CT) data (27). CTs are small, relatively stable geographic areas that usually have a population of less than 10,000 persons (27). Potential neighborhoods were subsequently confirmed with 2021 census data and selected based on relatively higher proportions of their population with the following characteristics: age 55 and older, experiencing marginalization regarding material resources (composite score of education levels, those receiving government transfer payments, income, and unemployment rates) (28), immigrants, and older adults (aged 65 and older) living below the low-income cutoff. In Hamilton, eight neighborhoods were selected that had higher proportions of older adults and high levels of health inequity compared to the other neighborhoods across the city. In collaboration with an organizational partner in Toronto (Dixon Hall), two neighborhoods in their catchment were identified as having older adults members living in areas with health inequitites and fewer existing supports who could benefit from the intervention.

#### Eligibility criteria

2.1.2

As a pragmatic trial, we chose broad inclusion criteria and will not exclude individuals based on existing chronic disease, comorbidities, or other factors that may impact attendance. All community-dwelling older adults (age 55 and older) living in a neighborhood selected for the study are eligible to participate in the study, with the only exclusion criteria being the inability to speak or understand English or Mandarin (at one site), the inability to walk 10 m without physical assistance from another person (assistive devices permitted), and lacking the capacity to consent to participate. Participants who do not speak or understand English or Mandarin (at one site) but have a family member/friend who can translate for them can participate with support.

#### Intervention

2.1.3

The intervention is described following the TIDieR checklist (29).

##### EMBOLDEN

2.1.3.1

**Theoretical underpinning**: The intervention and its core components are shaped by social cognitive theory targeting behavioral change through tailored and group-based approaches (30). An adapted experience-based co-design process with community-dwelling older adults and health and social service providers who were members of the SGC was used to refine and operationalize core intervention components (see below) (21). Qualitative research suggests co-design processes contribute to positive impacts at the participant, provider, and organizational levels (31). Our co-design process supported identifying key design features aligned with older adults’ priorities, delivery processes to match their preferences and ‘emotional touchpoints’ (i.e., maximizing positive experiences and addressing negative emotions that may be barriers to engagement). The co-design process used to engage the SGC has been evaluated. This included responses from a questionnaire, focus groups, and document analysis of meeting notes from 16 SGC meetings. Participants noted the strength of diversity within the SGC and engagement processes were perceived as inclusive and well-facilitated. The important impacts of the SGC in the preparation, execution and translational stages of EMBOLDEN were described by all participants, as well as the personal benefits of being involved as a member of the SGC (32).

**Core components:** The EMBOLDEN intervention will consist of usual care (see below) plus the following two core components: 12 weekly interactive group sessions and individually tailored 1:1 system navigation support. Both components will be delivered by the intervention team consisting of trained EMBOLDEN program facilitators who work in existing roles in community organizations and institutions (e.g., primary care interdisciplinary team members, municipal public health units, and municipal recreation departments).

As part of the program, we have engaged real-world providers who work for organizations that deliver similar types of programs, typically as one or occasionally two component(s) of the EMBOLDEN program. We offer the program in existing publicly funded facilities that operate within or nearby the neighborhoods (when a facility did not exist within the boundaries). We negotiated these partnerships and ensured alignment with their organizational mandates as part of the pragmatic trial to lay the foundation for sustainability.

Several adaptations to the intervention may be tailored to site-specific circumstances (e.g., language requirements and provider availability at partner organizations) while maintaining core intervention components; these adaptations are discussed below.

Core component #1—weekly group sessions: These group-based sessions will run each week for 12 sessions lasting approximately 120 min each. Group sessions will be delivered at an accessible, local community venue such as a recreation facility or community center located within or close to each priority neighborhood. Group sessions will focus on the following: (1) increasing knowledge, skills, and behaviors related to physical activity, healthy eating, and available community supports for older adults (including 30 min of facilitated physical activity delivered by a certified fitness instructor with experience and expertise working with older adults and interactive nutrition sessions led by the registered dietitian); (2) socialization activities to foster peer interactions and community connections, co-learning, and address social isolation; and (3) behavioral activation, goal setting, and skill-building to support independence and quality of life. The sessions will have a standardized and integrated curriculum to ensure core content of all curriculum threads is covered each week, with flexibility built into weekly topics and activities to allow the relative weighting and focus to be adapted to align with the interests and needs of a group (e.g., specific physical activities, interactive healthy eating activities, social activities, health promotion topics, community resources). Intervention participants will receive a Certificate of Completion at the end of the program.

Core component #2—system navigation: Up to three individually tailored, one-on-one sessions with a system navigator will be offered to participants virtually (via telephone or Zoom, according to participant preference). The sessions will be offered at the program’s beginning (~weeks 1–4 of group program), midpoint (~weeks 5–8) and end (~weeks 10–12). This facilitated system navigation support will be enabled by the Genie® system^1^ that we digitally mapped to each municipality’s local community information database (i.e., Red Book in Hamilton, 211 in Toronto). The Genie® system is an interactive, web-based self-management tool that maps participants’ social support network, elicits topics of interest (e.g., getting fitter, social activities, caregiving support), and supports individuals to connect with local programs and services, in alignment with their identified interests/priorities in a user-friendly “report.” During the encounter, the starts with gathering information about the participant’s demographics, including their postal code, to support later identifying resources located in geographic proximity to the participant. The facilitator then asks about the participant’s network that support them in their health and wellness goals, including informal and formal supports (e.g., health/social care providers), which acts as a visual aid to reinforce the person’s support network. The facilitator then gathers information about the participant’s interests and goals to provide them with resources, programs, and services in their community tailored to them. The facilitator enters participant’s data directly into the GENIE platform and can refer to the first encounter in subsequent sessions. The timing of the second and third individual system navigation sessions are flexible, according to participants’ expressed interests and needs. Participants will receive telephone or email system navigation session reminders, are free to opt out of these reminders, and will not be expected to reply to the messages unless they are unable to attend.

For any participants presenting with delirium or other emergent medical conditions during the study, the interdisciplinary intervention team would assess the situation and call for supports, if needed (e.g., family members, emergency responders).

**Interventionist training**: Intervention team members will receive 10–12 h of training on the curriculum (all components), facilitation skills, documentation (REDCap®), and system navigation software (Genie®). The intervention team is trained on ‘how to recognize signs of mental health distress’ and provided with relevant community resources and crisis supports to access, as needed. Through the orientation and training of these providers, we have strengthened capacity in the existing community-based workforce who work with older adults in these communities. While they are providing motivation and support within the EMBOLDEN program, they will continue to have these competencies when they return to their usual programming roles.

A training manual for delivering the EMBOLDEN program in English was developed and a manual to support delivery in Mandarin will be developed. Both will include detailed information for adaptations and tailoring all components to this linguistic and cultural group.

**Hamilton Mandarin site program adaptations:** One of the Hamilton sites will be comprised entirely of Mandarin-speaking older adults. The program will be modified in several ways to tailor the program to these participants, including language translation of all study documents and participant intervention materials, and delivery of all intervention components in Mandarin.

**Toronto sites program adaptations:** In response to limitations on resources and provider availability to deliver the system navigation component through an existing community service organization, lay community members experienced in connecting older adults with community resources will deliver this component and a physiotherapist working within a multi-service agency (versus primary care) was selected as the Program Coordinator at one site.

##### Usual care

2.1.3.2

These services consist of older adults engaging in self-care and independently connecting with existing health and social service supports within the community to the extent that they are aware of them, self-initiate to access them, and overcome personal and system-based barriers without intervention or support by the research and/or intervention team. These services may include concomitant care/interventions, which are permitted in this trial due to its pragmatic nature.

#### Pilot study

2.1.4

A pilot study was run to inform this trial. The primary aim was to determine the required sample size for this trial and to ensure that the recruitment procedures, data collection instruments and measures, and intervention components were feasible to deliver and acceptable to participants and providers. The pilot study was conducted over 9 weeks, delivered virtually (as it occurred during COVID and was subject to public health restrictions), and 10 participants were randomized (six intervention and four control, none involved in this trial). After finishing the pilot study, the participants were invited to give suggestions and feedback, which were incorporated into the trial design and this protocol. Pilot results informed the recruitment procedures (described below), confirmed that the intervention was feasible and acceptable to both participants and providers (with a strong preference for in-person delivery), helped determine the sample size for this trial, and resulted in the retention of all but one of the outcomes originally proposed (33).

#### Outcomes

2.1.5

##### Effectiveness

2.1.5.1

###### Primary outcome

2.1.5.1.1

The primary outcome is time spent doing moderate-to-vigorous physical activity (MVPA) measured in minutes/day at each of the three timepoints (t_1_ = baseline, t_2_ = 3-months, t_3_ = 6-months). This outcome was selected because physical mobility was a priority in the EMBOLDEN intervention based on co-design, funding agency priorities, and high-level evidence cites it as one of the most common measures used to evaluate the long-term effectiveness of physical activity interventions (34).

Mean minutes/day of MVPA at each timepoint will be estimated using heart-rate data captured by a smartwatch (TicWatch Pro 2 Ultra GPS), using two heart-rate-based equations:

1 Maximum heart rate (MaxHR): MaxHR will be estimated using a formula appropriate for older adults [207-(0.7xAge)] (35, 36), and samples will be classified as light, moderate or vigorous based on the following %MaxHR: very light/light (<64%), moderate (64–76%), vigorous (>76%) (37). The time spent with a heart rate in the moderate or vigorous zone will be calculated for each wear day in order to calculate an average min/day of MVPA for each timepoint.2 Heart rate reserve (HRR): also called the “Karvonen formula” (38, 39), this method uses %HRR to define physical activity intensity, where HRR = MaxHR – Resting HR (RestHR). MaxHR will be calculated as described above and RestHR will be calculated as the average of the daily minimum heart rate for 7 days. Samples will be classified as moderate/vigorous/light using the following formula: HRR × %Exertion, where moderate to vigorous intensity is % Exertion ≥40%. Samples in the moderate-vigorous categories will be aggregated and an average of minutes/day will be calculated for each timepoint as described above for MaxHR.

There is no clear guidance from the literature as to which approach is preferred, therefore, the change in the mean from baseline will be analyzed and reported for MVPA estimates from both algorithms.

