##### Smartwatch data

2.3.1.1

The watches are distributed to study participants in both groups by priority postal mail and returned to the research team through the same mechanism. Study participants in both groups (intervention, control) will be instructed to wear the smartwatch for 7 days prior to baseline (t_1_), and for the first 7 days of t_2_ (3 months) and t_3_ (6 months). Since the smartwatch is intended to collect objective data on physical mobility rather than serve as part of the intervention to incentivize/motivate it, all watches will be configured to allow participants to view only the time and not their activity data.

The checklist by Matthews et al. (68) will be used to ensure our design, implementation, and reporting are consistent with objective standards for the use of physical activity devices in population-based research. Table 3 provides our design and implementation decisions relating to the items in their checklist. We are primarily interested in the following mobility-related measures: heart rate (sampling rate: 1 Hz), accelerometer data (sampling rate: 50 Hz), and GPS data (sampling rate: upon movement or 5-min intervals).

**Table 3 tab3:** Checklist for design, collection and reporting of physical activity monitoring data.

Feature/characteristic	Criteria
Device Selection	The TicWatch Pro 3 Ultra GPS was selected to capture mobility-related data from participants. The primary reason for selecting this smartwatch over others was the ability to access the raw data. Raw mobility-related data of primary interest includes heart rate (sampling rate: 1 Hz), accelerometer data (sampling rate: 50 Hz), and GPS data (sampling rate: upon movement or 5 min intervals).
Reliability and validity of the device	The TicWatch Pro 3 Ultra GPS device is a high-quality smartwatch; its activity-related measures offer the reliability and validity of other smartwatches in its class (e.g., Fitbit, Garmin, Apple). (93)
Wearing location (on body)	Participants will be instructed to wear the watch on their non-dominant hand during waking hours and to charge the watch nightly.
Target sampling period	Participants will be instructed to wear the watch for 7 consecutive days prior to t_1_ (baseline), and for the first 7-days of t_2_ (3-months) and t_3_ (6-months).

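### The heart-rate-reserve rule for MVPA is printed without the resting heart rate and without saying how a sample is compared with it; taken literally as a cut-point, it falls below rest for most participants

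*Protocol article*

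**What the plan says.** Section 2.1.5.1.1 (Primary outcome) of the protocol article derives MVPA in minutes per day from smartwatch heart rate by two algorithms and reports results from both.

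The first uses the percentage of maximum heart rate. "MaxHR will be estimated using a formula appropriate for older adults [207-(0.7xAge"; the zones are "very light/light (<64%), moderate (64–76%), vigorous (>76" (per cent of MaxHR). MVPA therefore starts at 64% of MaxHR.

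The second uses heart rate reserve. It is "also called the “Karvonen formula", and "this method uses %HRR to define physical activity intensity, where HRR = MaxHR – Resting HR (RestHR". Resting heart rate comes from the watch: "RestHR will be calculated as the average of the daily minimum heart rate for 7 days". The classification step then reads: "Samples will be classified as moderate/vigorous/light using the following formula: HRR × %Exertion, where moderate to vigorous intensity is % Exertion ≥40" (per cent).

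Table 3 in section 2.3.1.1 refers back to section 2.1.5.1 for the algorithms and prints no other formula.

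**The concern.** The HRR is the distance between resting and maximum heart rate. Multiplying it by 40% gives the number of beats above rest at which moderate intensity begins. To obtain a heart rate with which a sample can be compared, RestHR must be added back; equivalently, the sample must be expressed as (HR − RestHR)/HRR. The printed step does neither, although the same paragraph names the Karvonen method and says that intensity is defined by %HRR.

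An analyst who compares each heart-rate sample directly with the printed product would apply a threshold below most people's resting heart rate. Table 3 determines daily wear time by counting heart-rate observations. If nearly every valid sample also counts as MVPA, HRR-based MVPA becomes nearly the same quantity as wear time, and the treatment contrast on that version of the primary outcome would compare how long each arm wore the watch.

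**Working it through.** **Inputs from the protocol article**
- MaxHR = 207 − 0.7 × age (section 2.1.5.1.1).
- HRR = MaxHR − RestHR (section 2.1.5.1.1).
- MVPA threshold on the HRR algorithm: 40% (section 2.1.5.1.1).
- MVPA threshold on the MaxHR algorithm: 64% of MaxHR (section 2.1.5.1.1).
- Minimum age 55, no upper limit (section 2.1.2).

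**Assumed input.** The document gives no resting heart rates. I take 50–80 bpm as the main range and show 40 bpm as an extreme.

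The plan states no cut-point in bpm, so there is no figure of its own to reproduce.

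**Step 1: cut-points (bpm)**

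| Age | MaxHR | RestHR (assumed) | HRR | Literal: 0.40 × HRR | With rest: RestHR + 0.40 × HRR | 0.64 × MaxHR |
|---|---|---|---|---|---|---|
| 55 | 168.5 | 50 | 118.5 | 47.4 | 97.4 | 107.8 |
| 55 | 168.5 | 60 | 108.5 | 43.4 | 103.4 | 107.8 |
| 55 | 168.5 | 80 | 88.5 | 35.4 | 115.4 | 107.8 |
| 70 | 158.0 | 50 | 108.0 | 43.2 | 93.2 | 101.1 |
| 70 | 158.0 | 60 | 98.0 | 39.2 | 99.2 | 101.1 |
| 70 | 158.0 | 80 | 78.0 | 31.2 | 111.2 | 101.1 |
| 85 | 147.5 | 50 | 97.5 | 39.0 | 89.0 | 94.4 |
| 85 | 147.5 | 60 | 87.5 | 35.0 | 95.0 | 94.4 |
| 85 | 147.5 | 80 | 67.5 | 27.0 | 107.0 | 94.4 |

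The literal cut-point runs from 27.0 to 47.4 bpm and is below RestHR in every row. With RestHR added, it runs from 89.0 to 115.4 bpm, the same region as the 94.4–107.8 bpm of the MaxHR algorithm.

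**Step 2: when the literal cut-point is below rest.** 0.40 × (MaxHR − RestHR) < RestHR is the same as RestHR > 0.40 × MaxHR / 1.40. The limits are:
- age 55: 0.40 × 168.5 / 1.40 = 48.1 bpm
- age 70: 0.40 × 158.0 / 1.40 = 45.1 bpm
- age 85: 0.40 × 147.5 / 1.40 = 42.1 bpm

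The limit falls with age, so a RestHR above about 48 bpm is enough at every eligible age.

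**Step 3: the exception.** At RestHR 40 the literal cut-point is 0.40 × 128.5 = 51.4 bpm at age 55 and 0.40 × 107.5 = 43.0 bpm at age 85. That is above rest, but only by 11.4/128.5 = 9% and 3.0/107.5 = 3% of the reserve, where 40% is meant.

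**Step 4: illustration of the share of samples classified as MVPA.** Heart rate was simulated as RestHR plus a gamma variable (shape 2.25, scale 8; mean 18 bpm above rest). This distribution is assumed.

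| Age, RestHR | Literal | With rest | 64% MaxHR |
|---|---|---|---|
| 55, 50 | 100% | 2.7% | 0.9% |
| 70, 60 | 100% | 6.1% | 5.0% |
| 85, 65 | 100% | 11.1% | 15.5% |

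The 100% follows by construction, because every simulated sample lies above RestHR and the literal cut-point lies below it. The other two columns show the order of magnitude at which the two sensible rules would agree.

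**The case against.** The best defence is that the text never says a raw heart rate is compared with the product. It gives a product without a comparator and then a criterion on the percentage of exertion. If that percentage is taken as the sample's own %HRR, (HR − RestHR)/HRR, then the 40% threshold is the right rule and the product is simply the increment above rest. The method's name and the reference to %HRR both point that way. This stands: the standard form was probably meant, and what is printed is an incomplete formula rather than evidence of a wrong analysis.

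A reader might infer that the trial will in fact report wear time as MVPA. The document does not support that. The analysis code is not shown, and the article condenses an approved protocol that is not at hand. A result coded this way would also be conspicuous beside the much lower MaxHR-based figure for the same people.

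A reader might also infer that every sample counts as MVPA for anyone above the limits in step 2. That is too absolute. RestHR averages daily minima, so on some days the minimum lies below it. At age 55 and RestHR 49 the literal cut-point is 0.40 × 119.5 = 47.8 bpm, and a day with a minimum of 46 bpm would have some samples under it. Essentially all is the defensible wording.

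Nor can the point be extended to the sample size: section 2.1.7 does not say which algorithm produced the pilot MVPA values.

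What the defence does not remove is that the article prints an explicit formula for one of the two versions of the primary outcome, that it cannot serve as a heart-rate threshold, and that nothing elsewhere in the article corrects it.

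**Conclusion.** The concern holds as an error in the printed outcome definition. The HRR rule lacks the resting term and does not state the comparison, which contradicts the method it names. If it were coded literally as a cut-point, the threshold would be roughly 50–80 bpm too low (by exactly RestHR), and that version of the primary outcome would nearly equal wear time.

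The size rests on an assumed RestHR of 50–80 bpm, and the literal threshold is below rest at any eligible age once RestHR exceeds about 48 bpm. The MaxHR version is not affected, and no sample-size, power or error-rate figure in the article is shown to depend on the rule. It still needs correcting, because this is the public specification against which the primary result will be checked.

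**What to change.** Replace the classification sentence in section 2.1.5.1.1 with: *A sample is moderate-to-vigorous if HR ≥ RestHR + 0.40 × (MaxHR − RestHR), equivalently (HR − RestHR)/HRR ≥ 40%.* Carry the same wording into the full protocol and the analysis plan if they repeat the printed formula, and confirm before analysis that the code uses this rule.

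The cost is one line of text and a code check. Section 2.3.1.1 says that heart rate is sampled at 1 Hz and that the watch was chosen for access to raw data, so classification can be rerun. No new data are needed, and randomisation and trial conduct are untouched.
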